**Fig. 1 Fig1:**
[figure not shown]
Study flowchart

### Eligibility criteria

The patients included in the study are: adult sedentary men and women who are 21–60 years old, who have diagnosed systolic HF, a left ventricular ejection fraction of less than 45% evaluated by echocardiogram, functional class II and III (New York Heart Association), forced expiratory volume in the first second (FEV_1_) of less than 80% predicted and/or FEV_1_/ forced vital capacity (FVC) ratio of more than 70% predicted, inspiratory muscle weakness with a maximum inspiratory pressure (MIP) of less than 70% of predicted value for age and gender, and clinical stability and who are ex-smokers of more than 5 years and who have no change in the class of medications within 3 months prior to the start of the study. The patients will be excluded if presenting unstable angina; myocardial infarction or previous cardiac surgery up to 3 months before the beginning of the study; chronic respiratory diseases; smokers; hemodynamic instability; or recent face trauma, nausea, or vomiting (or a combination of these). Individuals with orthopedic and neurological diseases that may make it impossible to perform cardiopulmonary testing and CR exercises are also to be excluded, as are patients who present psychological alterations that restrict them from responding to the questionnaire.

### Intervention

Individuals will be allocated into one of two groups: the control group and the experimental group. The control group will be submitted to the conventional CR protocol, and the experimental group will follow the conventional CR protocol associated with IMT. The two proposed exercise protocols will have a frequency of three times a week for a period of 12 weeks.

#### Experimental group: conventional CR + IMT

The CR protocol consists of a supervised exercise program divided into two phases—aerobic exercise and strength training—with a goal of three sessions per week for a total of 36 sessions in 12 weeks. During the aerobic exercise phase, patients will initially walk on a treadmill or pedal on a stationary bicycle for 15 to 30 minutes per session continuously in a heart rate zone corresponding to the first ventilatory threshold obtained on the ergospirometric test. The exercise duration will be increased to 30 to 35 minutes after six sessions. The strength training phase will subsequently be performed with incremental load for upper and lower limbs.

The IMT will be conducted by the participants themselves seven times a week after being instructed how to do it by the lead researcher. These sessions will occur six times a week in the home environment and once a week at the research site, at which time there will be readjustment to the load. The IMT duration will also be 12 weeks. Powerbreathe® Classic – Light Resistance (Powerbreathe International Ltd., Southam, UK) equipment with a nasal clip at an intensity of 30% of the MIP will be used to perform the training [11] and will be evaluated through digital manovacuometry [14]. Powerbreathe® will be used offering a linear pressure load with a load range ranging from 10 to 90 cm H_2_O, with increments of 10 in 10 cm H_2_O with each turn given to the adjustment valve, so we will do a half turn on the valve when the determined load does not reach exact values, which allows an increase of 5 cm H_2_O.

The daily training will be 30 minutes stratified into three sets of 10 minutes or two sets of 15 minutes. Individuals will receive a training control card (training diary) to be filled in each training series and taken weekly to the researcher responsible for control. During training, patients will be instructed to inhale until the air enters and to maintain a respiratory rate between 12 and 16 incursions per minute. In order to minimize the information bias for both groups, we will also conduct telephone distance monitoring for all the days when we do not have personal contact with the patients.

#### Control group: conventional CR without IMT “Sham”

The CR protocol is the same for the experimental group. Sham is performed in a manner similar to that of the experimental group—daily training of 30 minutes stratified in series of 10 or 15 minutes—but the intensity does not exceed 10% of the MIP, which is not configured as training of the inspiratory musculature.

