## Discussion

HF is a growing public health problem and has high morbidity and mortality rates [24]. This clinical trial is feasible and will be the first study to investigate the additional effects of IMT on CR, sympathetic activity, maximum and submaximal functional capacity, diaphragm mobility and thickness, and quality of life in patients with HF.

The IMT will be carried out through a validated instrument [25] and is suitable for this purpose. The device allows the training to be performed safely and unsupervised, but it has the limitation that it can be adjusted by only 10 cm H_2_O; thus, we will use approximate values in centimeters of water in an attempt to adjust this point. The results of this study will contribute to develop therapeutic strategies collaborating to elucidate whether the association of IMT with CR can induce clinical benefits for patients with HF.

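### As written, the sham ceiling of 10% of MIP and the device's 10 cm H2O minimum cannot both hold when MIP is below 100 cm H2O

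*Protocol article*

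**What the plan says.** In the Protocol article, the Control group section says that sham training follows the same daily pattern as the active training, "but the intensity does not exceed 10% of the MIP". It then states that such a load does not count as training of the inspiratory muscles.

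The Experimental group section says that Powerbreathe "equipment with a nasal clip at an intensity of 30% of the MIP will be used to perform the training". It describes the device "with a load range ranging from 10 to 90 cm H_2_O". One full turn of the valve changes the load by 10 cm H2O. For targets that fall between settings it adds: "so we will do a half turn on the valve when the determined load does not reach exact values", which it describes as allowing an increase of 5 cm H2O.

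The section on randomization, allocation and blinding gives the training device to all patients and has inspiratory strength re-measured weekly. No other sham device, removed spring or zero-load setting is described.

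The Eligibility criteria require a "maximum inspiratory pressure (MIP) of less than 70% of predicted value for age and gender". No lower limit for MIP is stated. The Manovacuometry section cites an equation for predicted MIP but does not give it.

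The Discussion says of the device that "it has the limitation that it can be adjusted by only 10 cm H_2_O", and that approximate values will be used for this reason. It does not mention the 10 cm H2O minimum.

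**The concern.** The sham ceiling is a percentage of each patient's own MIP, while the device minimum is a fixed pressure. In patients selected for weak inspiratory muscles, a fixed minimum is a large share of MIP, so the lowest stated setting can exceed the ceiling.

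The comparison rests on that ceiling. The stated hypothesis compares CR plus IMT with CR without IMT, and the control counts as CR without IMT only because its load is said to be too low to train the muscle. If control patients train above the ceiling, the trial compares two loads of inspiratory training. The expected effect is dilution of the difference in both primary outcomes (myocardial sympathetic activity and maximal functional capacity). A null result could not then be read as showing that IMT adds nothing to CR, and no later analysis can restore a contrast that was not delivered.

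**Working it through.** The article gives no sham load in cm H2O, so there is no stated figure to reproduce. The check uses these inputs:

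- sham ceiling 0.10 × MIP (Control group section)
- active target 0.30 × MIP (Experimental group section)
- device minimum 10 cm H2O, full turn 10, half turn 5 (Experimental group section)
- the training device for all patients (Randomization, allocation, and blinding)
- entry MIP below 0.70 × predicted, no lower limit (Eligibility criteria)

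**When can the ceiling be met?** The minimum respects the ceiling only if 10 ≤ 0.10 × MIP, that is MIP ≥ 10/0.10 = 100 cm H2O.

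**Who can have MIP of 100 or more at entry?** Since MIP < 0.70 × predicted, this needs predicted MIP > 100/0.70 = 142.9 cm H2O. The equation is not shown, so the predicted values below are assumptions chosen to span that threshold.

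| Predicted MIP (assumed) | Eligible MIP | 10% ceiling |
|---|---|---|
| 80 | below 56 | below 5.6 |
| 100 | below 70 | below 7.0 |
| 120 | below 84 | below 8.4 |
| 140 | below 98 | below 9.8 |
| 150 | below 105 | below 10.5 |

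**How far above the ceiling is the minimum, and what contrast remains?** The intended ratio of active to sham load is at least 30/10 = 3. The fifth column divides the unrounded active target by the 10 cm H2O minimum, so it needs no rounding rule. The last column assumes that the active load is set to the nearest 5 cm H2O.

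| MIP (cm H2O) | 10% ceiling | 10 cm H2O as % of MIP | 30% target | Target ÷ 10 | Nearest-5 setting ÷ 10 (assumed) |
|---|---|---|---|---|---|
| 30 | 3.0 | 33.3 | 9.0 | 1.0 (at minimum) | 1.0 |
| 40 | 4.0 | 25.0 | 12.0 | 1.2 | 1.0 |
| 50 | 5.0 | 20.0 | 15.0 | 1.5 | 1.5 |
| 60 | 6.0 | 16.7 | 18.0 | 1.8 | 2.0 |
| 70 | 7.0 | 14.3 | 21.0 | 2.1 | 2.0 |
| 80 | 8.0 | 12.5 | 24.0 | 2.4 | 2.5 |
| 90 | 9.0 | 11.1 | 27.0 | 2.7 | 2.5 |
| 100 | 10.0 | 10.0 | 30.0 | 3.0 | 3.0 |

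**When would the arms have the same load?** The active target is at or below the minimum when 0.30 × MIP ≤ 10, that is MIP ≤ 33.3 cm H2O. Both arms are then at 10 cm H2O whatever the rounding rule. Under the assumed nearest-5 rule, targets below 12.5 are also set to 10, which extends this to MIP < 12.5/0.30 = 41.7. If targets are rounded up instead, MIP 40 gives a target of 12 and a setting of 15 against 10, and the limit stays at 33.3.

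**What if a half turn could give 5 cm H2O?** The ceiling would then be met from MIP = 5/0.10 = 50 upward and would still fail below 50. The equal-load limit would fall to 5/0.30 = 16.7.

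**The case against.** The best defence is that the text sets a ceiling, which a no-load arrangement would satisfy, and that a condensed article may leave the practical sham set-up to the full protocol. This stands to the extent that the article does not show what control patients actually received. A reader might infer that they are in fact trained above 10% of MIP, but the documents support only that the stated ceiling and the stated range conflict below MIP 100. It does not remove the point, because the article states both figures, gives all patients the device and describes no other arrangement.

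Second, the half turn might supply 5 cm H2O. The stated range begins at 10 and the half turn is described as an increase, so the text does not support this. It would in any case leave the conflict in place below MIP 50.

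Three stronger readings are tempting and should not be adopted:

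- *The ceiling fails for every patient.* A patient with predicted MIP above 142.9 could enter with MIP of 100 or more. The entry criterion also limits MIP only at entry, and MIP may rise over the 12 weeks.
- *The arms get the same load up to MIP of about 41, or 50 with 10 cm H2O steps.* These limits depend on nearest-step rounding, which the article does not state. Only MIP of about 33 or less follows without it, given the stated minimum.
- *The Discussion contradicts the half-turn procedure.* It names the 10 cm H2O step as a limitation and then says that approximate values will be used to deal with it. That can be read together with the half turn as the workaround.

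It is also fair to say that at MIP 80 to 90 most of the intended contrast survives (2.4 to 2.7 against 3), and that no MIP distribution is given.

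**Conclusion.** The contradiction holds on the article's own figures. With the stated device minimum, the sham ceiling cannot be met when MIP is below 100 cm H2O. At entry this covers every patient with predicted MIP of about 142.9 cm H2O or less. These two thresholds rest only on the stated ceiling, range and entry criterion, and on the absence of any other described sham set-up.

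The excess over the ceiling is modest near MIP 90 and reaches two and a half times the ceiling at MIP 40. Equality of the arms is firm only at MIP of about 33 or less. Such patients are eligible, but how many there are is unknown, as is the overall share affected. The expected direction is a smaller contrast between arms, most in the weakest patients, and a control that cannot be assumed to be non-training. The control rule cannot be delivered as described, and this bears on how a null result may be read, so the text needs correcting.

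**What to change.** Reconcile the Eligibility criteria, the Experimental group section and the Control group section so that the sham ceiling and the device range can both hold over the MIP range enrolled. Which of them gives way is for the sponsor to decide; no load is proposed here.

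At each weekly adjustment, record the set load in cm H2O and as a percentage of that week's MIP, in both arms. Keep this record with the researcher who sets the loads, who already knows the allocation, so that blinding is not weakened. Report it by arm at the end, and describe the control by the load actually delivered rather than as 10% of MIP or less.

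The cost is a protocol clarification and one record per patient per week, built on the strength measurement and load adjustment already planned. Recruitment was under way when the article was written, so loads already set would need to be recovered where they were noted. The downside is that the control may have to be called low-load rather than inert, and the conclusion worded as a comparison of two loads.

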### Criteria for discontinuing or modifying the allocation

The criteria for discontinuing or modifying the allocation are worsening of symptoms, clinical instability, change in the class of medications, and emergence of serious infectious or viral diseases (or both) which are difficult to control.

### Strategies to improve adherence

The strategies to improve adherence are weekly educational lectures with topics related to the pathophysiological, nutritional, and medical aspects of HF and frequent connections to encourage rehabilitation and IMT daily as well as a training control diary that will be delivered to each participant.

### Evaluated outcomes

The participating individuals will be evaluated on the first day of evaluation by collecting their clinical history, applying the quality-of-life questionnaire, and reading the echocardiogram. Then they will be submitted to an anthropometric evaluation (height and weight through a digital scale with anthropometer [model W300, Welmy, São Paulo, Brazil] with a capacity of 300 kg, precision of 50 g, and an anthropometer with limit of 2 m and body mass index by dividing body weight by height squared), evaluation of vital signs through a multiparameter monitor (2023, Dixtal, Manaus, Brazil), evaluation of pulmonary function through spirometry, and evaluation of respiratory muscle strength through manovacuometry. Ultrasonography will be performed on the second day to measure the diaphragm muscle thickness and mobility (secondary outcome endpoint), and maximum functional capacity (primary outcome) will be evaluated by a responsible medical professional.

The Glittre-ADL test will be performed on the third day for submaximal measurement of functional capacity (secondary outcome). Finally, the patients will be referred to a specialized hospital on the fourth day for myocardial scintigraphy (primary outcome). After all the evaluation procedures have been carried out and recorded on the corresponding file, the participants who are already randomly allocated will start their respective IMT protocols associated with CR; then the subjects will be submitted to the same evaluation process at the end of 36 sessions, along with a question that measures the degree of satisfaction with the treatment. Figure 2 and the checklist provide an overview of standardized items for clinical trials according to Standard protocol items: Recommendations for interventional trials (SPIRIT) [15].

**Fig. 2 Fig2:**
[figure not shown]
Standard protocol items: recommendations for interventional trials (SPIRIT) flowchart

### Randomization, allocation, and blinding

The subjects will be randomly assigned to groups through the website www.randomization.com in regard to the following protocols: control group (CR and “Sham” IMT) and experimental group (CR and IMT at 30% MIP). Then the allocation will be performed through numbered opaque envelopes by the researcher responsible for the weekly adjustment of the Powerbreathe load and they will only open the envelope corresponding to the patient at the time of the first adjustment. The entire randomization and allocation process will be carried out exclusively by the collaborating researcher, and the researcher will remain confidential until the end of the study. No other researcher or patients will be aware of which group they belong to, including the same one.

All of the patients will receive the training device and will have inspiratory muscle strength re-evaluated weekly to ensure patient masking, not being aware of whether the load is being increased or not. The device contains a protective cover that makes it impossible to visualize the imposed load. In addition, if the patient reports that the training is light, the researcher will tell them that it is natural and occurs as a result of training progression and improvement in muscle strength.

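### The researcher who runs the randomisation also opens the envelopes and sets the load, so the envelopes do not conceal the sequence from that person, and the masking sentence needs rewording

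*Protocol article*

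**What the plan says.** All but one of the statements below stand in the Protocol article under Randomization, allocation, and blinding.

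- Source of the sequence: "The subjects will be randomly assigned to groups through the website www.randomization.com".
- Who allocates: the step is done through "numbered opaque envelopes by the researcher responsible for the weekly adjustment of the Powerbreathe load".
- When the envelope is opened: "they will only open the envelope corresponding to the patient at the time of the first adjustment".
- Who is responsible overall: "The entire randomization and allocation process will be carried out exclusively by the collaborating researcher".
- Who is masked: "No other researcher or patients will be aware of which group they belong to, including the same one".

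Under Evaluated outcomes, once the baseline tests are finished, "the participants who are already randomly allocated will start their respective IMT protocols associated with CR".

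The study is labelled double-blind in the Abstract and under Study design.

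**The concern.** Envelope concealment works by separation: whoever opens the envelope must not have had access to the list. Here the article gives the list and the opening to the same person. If that person can also influence which patient starts next, or when, patients can be steered towards an arm. A later analysis cannot repair that.

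A second matter concerns the masking sentence. Its closing words, taken literally, extend unawareness to the very researcher who opens the envelope and sets an arm-specific load. A reader then cannot tell who is masked in a trial presented as double-blind.

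**Working it through.** No arithmetic applies. The article states no sample size (it is to be calculated from the first 20 patients) and gives no figure that bears on concealment. The check is a comparison of the statements.

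**1. Is it one person?** Allocation is performed "by the researcher responsible for the weekly adjustment of the Powerbreathe load". Two sentences later the entire process, randomisation and allocation together, belongs exclusively to the collaborating researcher. Both statements can be true only if the load-adjuster and the collaborating researcher are the same person. If they are two people, the word for exclusivity is wrong and the section contradicts itself. Either way the text needs correction.

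**2. Does this person have the sequence?** The sequence comes from a website. Because the whole of randomisation, and not only allocation, is given to this researcher alone, the text leaves no room for a separate generator of the list or preparer of the envelopes. It does not say whether the researcher reads or keeps the list.

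**3. What do the envelopes then protect?** The rule on the moment of opening is meant to keep the opener ignorant until the first load adjustment. It cannot do that for someone who produced the sequence. It can still keep the sequence from anyone else, including a separate recruiter.

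**4. Can access lead to selection?** Only if the person affects enrolment, patient numbering or start date. The article does not give them any of these tasks. It also does not keep them away from any of them.

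**5. Is the masking sentence consistent with the role?** The experimental arm trains "at an intensity of 30% of the MIP will be used to perform the training"; the section on the control group caps the sham load at 10% of MIP. Whoever sets these loads weekly must know the arm. The first half of the masking sentence speaks only of other researchers and of patients, and fits an unmasked operator. The last four words, read literally, do not.

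**6. When is assignment known?** Evaluated outcomes describes patients as allocated by the time the baseline tests end. The randomisation section puts envelope opening at the first adjustment. The two agree if a numbered envelope is tied to the patient early and opened later, but the article does not say so. The order of numbering, baseline testing and opening is therefore not fixed.

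**The case against.** The strongest reply is that concealment chiefly guards against whoever recruits and judges eligibility, and the article does not give the load-setter either task. Patients are recruited at reference centres (Ethical aspects), and entry rests largely on measured thresholds (Eligibility criteria). Training begins only after four days of evaluation, so little room is left to choose who enters. Other roles are partly separated: a medical professional evaluates maximal capacity, and scintigraphy takes place at a specialised hospital. A condensed article may also leave enrolment and numbering to the full protocol. Finally, the last words of the masking sentence have no clear antecedent; they may be a translation slip, or may mean only that patients do not know their own group.

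Much of this stands. A reader might infer that the envelopes conceal nothing, that every assignment is known in advance, or that this step is the only guard against selection. The documents support none of the three: the envelopes may work against a separate recruiter, the article does not say that the researcher consults the list, and the entry criteria and baseline assessment also limit selection. Nor is an unmasked load-setter a fault, since someone must set the load.

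What the reply does not remove is the stated arrangement. The article does not merely omit a list generator; it assigns the whole process to one person, and a fuller document that separated the roles would contradict it.

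**Conclusion.** The point holds in a limited form. As described, the envelopes do not conceal the sequence from the researcher who runs the randomisation, opens them and sets the load. Selection through patient order or start date is a risk left open and is not demonstrated.

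Its size cannot be derived from the article. It is zero if this person never influences who starts and in what order; otherwise it would not be reliably detectable afterwards. The conclusion rests on reading the load-adjuster and the collaborating researcher as one person, which the wording on exclusivity requires.

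The masking sentence is a matter of wording: read literally it conflicts with the load-setter's role, and it should be corrected even if it is only a slip. This is an inexpensive improvement to make while recruitment is open, not a defect shown to have biased the trial.

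**What to change.** For patients still to enter (Trial status gives recruitment as open, with closure forecast for December 2020):

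1. Have an existing team member without patient contact generate the remaining sequence and seal the numbered envelopes.
2. Have the load-setting researcher open the next envelope only after baseline is complete and the patient number is fixed.
3. Reword the masking sentence to say that the load-setter is unmasked and takes no part in enrolment or outcome assessment, and drop its closing words.
4. Reconcile the description of patients as allocated before training, under Evaluated outcomes, with envelope opening at the first adjustment, so that the order of numbering, baseline and opening is explicit.

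The cost is a short task for a colleague and a few sentences. The drawback is a change of list during recruitment, which must be documented and handled so that numbering and balance between arms are not disturbed. If the roles are already separate in practice, no new list is needed and correcting the sentences is enough.
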